### Exclusion and Non-qualifiers

The online questionnaire is built in three modules: A socioecological module; a module specific for men having sex with other men; and a module on HIV. Respondents must complete a module and click on 'next' in order to have her/his responses recorded. Any respondent leaving the survey before completing a module is *de facto* excluded from the survey. Respondent choosing to click on the 'exit' button are also excluded from the survey.

To increase the quality of the dataset, the research team will construct discrepancy flags which indicate whether respondents had supplied inconsistent data in different areas.

Non-qualifiers are respondents who did not meet the criteria for inclusion in the study. Non-qualifying cases include:

- Consent not provided
- Not providing a numeric value for age
- Not providing an age of 18 or higher
- Not belonging to any LGBTI groups

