### Non-respondents

Reflecting the experience of non-respondents is a challenge in such survey where participants are responding on a voluntary and anonymous basis. The proposal acknowledges this limitation. The report will be careful in extrapolating the findings. The report will mention the number of non-

respondents, i.e. people who did not meet the eligibility criteria and people who did not complete the survey.

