- ☐ 1 lowest social standing in my community

44. You would say you live in:

- ☐ a major city
- ☐ a medium- or small-size city
- ☐ a village
- ☐ a farm or an isolated house

45. People are different in their sexual attraction to other people. Which best describes your feelings? are you...

- ☐ attracted to other men or gay
- ☐ attracted to other women or lesbian
- ☐ attracted to both men and women or bisexual
- ☐ Straight or heterosexual
- ☐ I don't know

*Note: respondents answering 1 (gay), 3 (bisexual) or 5 (I don't know) will be offered to complete module 2*

*Respondents answering 2 (lesbian) or 4 (straight) will be redirected to question 61 (do you know your HIV status?)*

[ module 2 for gays, bisexuals, transgenders or men attracted to other men ]

exit

The following few questions are more specific for gay, bi, transgender and men attracted to other men

☐ OK *(click is required)*

An exit button is always available at the beginning of each module. Respondent can always scroll back to it

[Section on HIV prevention and exposure to HIV infection]

46. In the past 3 months, with how many **different** sexual partners did you have **anal sex without any kind of HIV prevention method**? That is without condoms, PrEP or an undetectable HIV viral load?
- ☐ 0
  - ☐ 1, steady
  - ☐ 1, casual
  - ☐ 2
  - ☐ 3 to 10
  - ☐ more than 10
  - ☐ Does not apply to me
47. Thinking about your last **anal sex partner without any kind of HIV prevention method** (that is without condom, PrEP or an undetectable viral load), how did it go?
- ☐ my partner fucked me (I was receptive)
  - ☐ I fucked him/her (I was insertive)
  - ☐ I both fucked and got fucked (I was both receptive and insertive)
  - ☐ does not apply to me
48. Thinking about your last **anal sex partner without any kind of HIV prevention method** (that is without condom, PrEP or an undetectable viral load), did you know his HIV status? tick as many as apply
- ☐ I didn't ask
  - ☐ s/he's HIV negative
  - ☐ s/he's HIV positive and I don't know his/her viral load
  - ☐ s/he's HIV positive AND undetectable
  - ☐ I was on PreP
  - ☐ s/he was on PreP
  - ☐ I don't remember
  - ☐ I had more than one partner and I do not know everyone's HIV status
  - ☐ does not apply to me

49. In the last 3 months, how much of the sex you've had with men has been under the influence of alcohol or any other drug?

- ☐ none of it
- ☐ almost none of it
- ☐ less than half
- ☐ about half
- ☐ more than half
- ☐ almost all of it

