**(Thank you message)**

*Thank you very much for your support.*

*Sign up to get the results of this study and participate in future studies, your information is completely anonymous, any IP address is decoupled, encrypted and deleted at the end of the study. [https://lgbt-token.org/research\\_signup](https://lgbt-token.org/research_signup) You may share the survey via: <https://www.research.net/r/LGBTHappinessResearch>*

*Get tested for HIV regularly. For more information: <https://hornet.com/about/know-your-status/>*

(Only participant who answered I'm HIV positive are offered to participate to module 3 below)

exit

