### Module 3: HIV-related stigma and discrimination

If you are HIV-positive, you may face stigma. Let's talk about it

Choose how you feel about each statement. We understand some questions might sound disturbing. Please share your experience. It will help to create a more inclusive environment for everyone

An exit button is always available at the beginning of each module. Respondent can always scroll back to it

☐ OK (click is required)

62. I am not as comfortable as I used to be in dating since I learned I have HIV

- ☐ strongly agree
- ☐ agree
- ☐ disagree
- ☐ strongly disagree
- ☐ I don't know

63. I disclosed my HIV status on my online profile in the main app I'm using

- ☐ yes
- ☐ no

64. If no, is there any reason you don't mention your HIV status? (tick as many as apply)

- ☐ I revealed it before and couldn't meet anybody
- ☐ I'm afraid of rejection
- ☐ I say I am looking for safe sex (like with a condom) and I do not need to tell them my HIV+ status
- ☐ I don't need to mention it
- ☐ I'm undetectable
- ☐ I don't want to mention it
- ☐ other
- ☐ does not apply to me (I disclosed my HIV+ status on my profile)

65. I changed the way I have sex since I know I'm HIV positive

- ☐ yes
- ☐ no
- ☐ I don't know
- ☐ does not apply

66. Since I've known that I'm HIV-positive, I have sex with:

- ☐ people regardless of their HIV status
- ☐ only HIV-positive partners
- ☐ I don't have sex anymore
- ☐ does not apply

67. Some people avoid touching me once they know I have HIV

- ☐ strongly agree
- ☐ agree
- ☐ disagree
- ☐ strongly disagree
- ☐ I don't know

68. People I care about stopped contacting me after learning I have HIV

- ☐ strongly agree
- ☐ agree
- ☐ disagree
- ☐ strongly disagree
- ☐ I don't know

69. I have lost friends by telling them I have HIV

- ☐ strongly agree
- ☐ agree
- ☐ disagree
- ☐ strongly disagree
- ☐ I don't know

70. Telling someone I have HIV is risky

- ☐ strongly agree
- ☐ agree
- ☐ disagree
- ☐ strongly disagree
- ☐ I don't know

71. I work hard to keep my HIV a secret

- ☐ strongly agree
- ☐ agree
- ☐ disagree
- ☐ strongly disagree
- ☐ I don't know

72. I am very careful whom I tell that I have HIV

- ☐ strongly agree
- ☐ agree
- ☐ disagree
- ☐ strongly disagree
- ☐ I don't know

73. People with HIV are treated like outcasts

- ☐ strongly agree
- ☐ agree
- ☐ disagree
- ☐ strongly disagree
- ☐ I don't know

74. Most people believe a person who has HIV is dirty

- ☐ strongly agree

- ☐ agree
- ☐ disagree
- ☐ strongly disagree

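### Read literally, the exit rule excludes HIV-positive respondents after they have reported their status, which lowers self-reported prevalence; the protocol must say whether submitted modules are kept

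*Protocol*

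**What the plan says.** Three sentences under Exclusion and Non-qualifiers (protocol, Sample size section) govern who is kept:

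- Recording: "Respondents must complete a module and click on 'next' in order to have her/his responses recorded".
- Drop-out: the sentence beginning "Any respondent leaving the survey before completing a module is" ends by declaring that person de facto excluded from the survey.
- Exit: "Respondent choosing to click on the 'exit' button are also excluded from the survey".

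Appendix 1 shows where these rules apply. The note "An exit button is always available at the beginning of each module" is printed at modules 1, 2 and 3. After Q45, "Respondents answering 2 (lesbian) or 4 (straight) will be redirected to question 61"; the others are offered module 2. Everyone is meant to reach Q61 (HIV status), which is followed by a PREV and a DONE choice. Then "Only participant who answered I'm HIV positive are offered to participate to module 3 below". Module 3 opens with an exit button and the warning "We understand some questions might sound disturbing".

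The Non-respondents section promises the number of non-respondents, meaning "people who did not meet the eligibility criteria and people who did not complete the survey". It does not promise a split by module or by HIV status.

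**The concern.** The two exclusion sentences remove the person from the survey. Neither says that the loss stops at the module being left. A respondent who reports being HIV-negative, not knowing, or not wanting to answer has nothing further to complete after Q61. One who reports being HIV-positive meets a further exit button and a further set of questions. If the rule is followed as worded, being dropped at that stage depends on the answer that defines the outcome.

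The Abstract makes self-reported HIV prevalence an aim, and the Sample size section aims at sound modelling of the correlates of HIV infection among the participants. Selection on HIV status after the question has been answered distorts the first directly, and may distort the second. The multiple imputation mentioned in the Sample size section cannot repair this if the whole record is out. The planned correction in the Limitations section concerns differential internet access and use, not this loss.

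**Working it through.** **1. The question counts.** The Questionnaire development section gives 45, 15 and 22 questions for modules 1, 2 and 3. By the numbering in Appendix 1:

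- Q1–45: 45 questions, agrees.
- Q46–60: 60 − 46 + 1 = 15, agrees.
- Q61–82: 82 − 61 + 1 = 22, agrees only if Q61 belongs to module 3.
- Q62–82: 82 − 62 + 1 = 21, which is what Appendix 1 prints after the module 3 exit.

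The count therefore places Q61 in module 3, while the layout places it before module 3. This decides with which module HIV status is recorded.

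**2. Who can be excluded once past Q61, on the literal reading.**

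| Answer at Q61 | Further module | Further exit or unfinished module possible |
|---|---|---|
| HIV-negative, does not know, prefers not to answer | none | no |
| HIV-positive | module 3, Q62–82 | yes |

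A person in the second row has by then answered module 1 and Q61, and module 2 if routed there.

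**3. Effect on prevalence.** Let p be the share who report being HIV-positive at Q61, and e the share of those excluded at module 3 by exit or drop-out. For simplicity, the denominator is everyone who answers Q61.

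Observed prevalence = p(1 − e) / [p(1 − e) + (1 − p)]

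The protocol gives neither p nor e, so both are assumptions. For p = 15% and e = 20%: 0.15 × 0.80 = 0.12, and 0.12 / (0.12 + 0.85) = 0.12 / 0.97 = 12.4%. Over a range:

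| p | e = 10% | e = 20% | e = 30% | e = 50% |
|---|---|---|---|---|
| 5% | 4.5% | 4.0% | 3.6% | 2.6% |
| 10% | 9.1% | 8.2% | 7.2% | 5.3% |
| 15% | 13.7% | 12.4% | 11.0% | 8.1% |
| 20% | 18.4% | 16.7% | 14.9% | 11.1% |

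The direction does not depend on the assumptions: any e above zero lowers the figure.

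**4. Effect on an association with HIV status.** Let e1 and e0 be the excluded shares among exposed and unexposed HIV-positive respondents. Only the two HIV-positive cells of the 2 × 2 table shrink, so the odds ratio is multiplied by (1 − e1) / (1 − e0).

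- e1 = e0 = 20%: 0.80 / 0.80 = 1, no bias.
- 20% and 10%: 0.80 / 0.90 = 0.89.
- 30% and 10%: 0.70 / 0.90 = 0.78.
- 40% and 10%: 0.60 / 0.90 = 0.67, which turns a true odds ratio of 1.5 into 1.0.
- 10% and 20%: 0.90 / 0.80 = 1.13, a bias the other way.

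Both the existence and the direction of this bias depend on how leaving relates to the exposure, which the protocol does not show.

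**5. If submitted answers, Q61 included, are kept.** Then e = 0 for HIV status and for all variables of modules 1 and 2. Observed prevalence equals p, the multiplier is 1, and only module 3 items are missing.

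**The case against.** The best reply is that the protocol does not say that completed modules are discarded. Answers are recorded at the end of each module, de facto can be read as a consequence of non-recording, and the exit sentence follows with *also*. Read in that order, exit may cost only the current module. This reading is open, and a reader who concludes that completed modules are certainly lost goes further than the text. But the exclusion is from the survey, nothing says that a recorded module survives a later exit, and the Non-respondents section counts those who did not complete the survey as non-respondents. The ambiguity stands.

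Second, DONE leads to the thank-you message, and that message is printed before module 3. Some HIV-positive respondents may be able to finish at Q61 and decline module 3 without clicking exit. The routing is not clear enough to rely on, but it means that e is not simply the share who decline module 3.

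Third, exit may be meant as withdrawal. The consent section promises withdrawal at any time, and the mailbox route in the monitoring section asks the person to reveal an IP address, so exit may be the only fully anonymous way out. Deleting answers on withdrawal is defensible. The protocol does not separate it from declining one more module.

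Fourth, a reader might infer that the association between stigma and HIV is biased toward the null. The documents do not support that as a finding. The stated research question concerns homophobic climate, which is asked about mainly in modules 1 and 2. HIV stigma in module 3 is asked only of HIV-positive people, so it cannot be an exposure for HIV status. That those who avoid module 3 are also more exposed to homophobia is plausible but assumed.

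Finally, the protocol disclaims representativeness, foresees drop-out by people afraid to share their HIV status, and will report the number of non-completers. This tempers the practical weight but does not cure a loss that depends on the outcome among the survey's own participants.

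**Conclusion.** The point holds as a defect of wording with a definite consequence on the literal reading. The exit and unfinished-module rules are not confined to the current module, and only respondents who report being HIV-positive can fall under them once past Q61. Self-reported prevalence is then too low whenever any of them leave at module 3. The size is unknown: 15% becoming 12.4% rests on an assumed prevalence and an assumed 20% loss, and should not be read as an estimate. Bias in associations needs the further condition that leaving depends on the exposure. The milder reading would remove the problem for everything recorded before module 3, provided that Q61 is recorded by then; the conflict over the 22 questions leaves that unsettled. Since the protocol itself fixes the rule, and answers not retained at collection cannot be recovered by later analysis, this should be settled before the survey opens.

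**What to change.** Amend Exclusion and Non-qualifiers to state that:

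1. Every completed and submitted module is kept for each eligible, consenting respondent.
2. Q61 is recorded before module 3 is offered. Reconcile the stated 22 questions for module 3 with the Appendix 1 layout, which gives 21. Without this, keeping completed modules might still lose HIV status.
3. Clicking exit, or dropping out, at a later module makes only that module missing. The rule must cover both routes.
4. Only an explicit withdrawal request deletes earlier answers.

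In the Non-respondents section, add the numbers reaching and completing each module, by HIV status where known, and separate ineligible people from non-completers.

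The cost is a few sentences and a check that the survey tool stores answers this way. No extra respondents or questions are needed. A separate anonymous button to withdraw and delete answers would be desirable, but it is optional: it changes an ethics-reviewed questionnaire, so it needs ethics notification and translation into the listed languages.

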### Non-respondents

Reflecting the experience of non-respondents is a challenge in such survey where participants are responding on a voluntary and anonymous basis. The proposal acknowledges this limitation. The report will be careful in extrapolating the findings. The report will mention the number of non-

respondents, i.e. people who did not meet the eligibility criteria and people who did not complete the survey.

#### m) Compensation of immediate medical or other assistance

This research is non-medical by nature and any medical or other assistance is unlikely. Still, we guarantee engagement and will create a mailbox representing the participating agencies to address any query and/or event related to this survey.

#### n) Incentives offered to participants

We do not use any type of incentives in this research.

#### o) Any information that will be provided to participants following their participation

The following elements are provided to respondents before they leave the survey:

- A thank you message for their participation and reminder of the anonymity of the survey;
- A weblink to the LGBTI Foundation where additional information on the survey, periodical updates, the general findings and next steps will be provided;
- An advocacy message encouraging participants to get tested for HIV infection.

The survey being anonymous, and the IP addresses being decoupled and encrypted automatically during the time the survey is online (3 months), there is no possibility to provide further direct information to participants after their completion of the questionnaire.

#### p) Limitations of the survey

This survey will be performed online. This channel is a demonstrated channel enabling higher number of respondents among hard-to-reach populations, faster recruitment, lower operational cost, and greater level of anonymity provided to participants. There are nevertheless limitations that should be acknowledged.

First is the statistical representativity of the survey. There is a selection bias in using social media and social networks. We will apply available techniques to correct for the bias that results from differential access to, and use of, the internet. Like other surveillance for key populations, the survey does not aim of a nationally representative sample of the LGBTI population of a said country.

Second is the access to the internet. Some members of the LGBTI community in low- and middle-income countries may face financial or material constraints to access the internet and thus the survey. UNAIDS Country teams will share the link of the survey with local LGBTI networks, encouraging them to see how they can facilitate an internet access to participants from their community, but it should be acknowledged that members of the LGBTI groups might not be represented.

The third limitation relates to the possible variations between languages. When available, we used validated translations of questions. When translations were not available, we made sure the translations were as close as possible from the original English version. This was achieved by performing translation and retranslation to English as proofreading. Despite of that, the specificities of the different languages make it almost impossible to ensure an exact correspondence. For

example, languages such as Japanese are highly contextual and situational and will thus require more words to describe “being comfortable”.

Finally, due to anonymity, self-reported responses such as country of residence or age cannot be verified by other means. In addition to the informed consent, the question on the age includes the choice “under 18”. Respondents selecting this answer will be considered as non-qualifiers.

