- contact information and procedures for contacting the investigators in case of further queries and/or questions.

Only 18+ year-old participants can participate in the survey provided an informed consent. Participants are required to acknowledge their informed consent to enter the survey by clicking on the "OK" button (question 1, mandatory).

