## Appendix 1: Online Questionnaire

2. What sex were you assigned at birth?

- ☐ intersex / ambiguous  
☐ female  
☐ male

3. How do you define your gender identity? (tick as many as apply)

- ☐ man  
☐ trans man (female to male)  
☐ trans woman (male to female)  
☐ woman  
☐ non-binary gender (Third gender, Hijra)

4. How do you afford your hormones therapy or sex affirmation surgeries? (tick as many as apply)

- ☐ does not apply to me  
☐ most of it is covered by the medical scheme of my country  
☐ my private health insurance covers most of it  
☐ from my own pocket  
☐ I'm working extra hours to afford it  
☐ I'm doing sex work to afford it  
☐ I regularly sacrifice a meal to pay for it  
☐ I can't afford it  
☐ I don't need / don't want hormones or sex affirmation surgery for the time being  
☐ it is illegal in my country  
☐ other

5. How masculine or feminine are you perceived to be by those around you?

- ☐ very masculine  
☐ masculine  
☐ neither masculine or feminine  
☐ feminine  
☐ very feminine

exit

An exit button is always available at the beginning of each module. Respondent can always scroll back to it

6. What country do you currently live in? Drop down menu
7. Which of the following best reflects why you live in this country: (tick as many as apply)
- ☐ was born here, or my parents moved here
  - ☐ to study
  - ☐ to work
  - ☐ to follow a partner
  - ☐ to live more openly as gay/bi/lesbian/trans
  - ☐ to seek asylum
  - ☐ I came as a refugee
  - ☐ other
8. How old are you? Drop down menu
9. Would you say that you are open (out) as gay, lesbian, bisexual, or trans [answer 1 for not at all open (in) and answer 5 for open (out) to all or most people, you know], or answer some place in between]:
- ☐ 1 not at all open (*in*)
  - ☐ 2
  - ☐ 3
  - ☐ 4
  - ☐ 5 open (out) to all or most people I know
10. In general, would you say that your health is
- ☐ excellent
  - ☐ very good
  - ☐ good
  - ☐ fair
  - ☐ poor

*[Section on wellbeing and happiness (note: text in blue does not appear in the questionnaire)]*

11. On the whole, I am satisfied with myself.
- ☐ strongly agree
  - ☐ agree
  - ☐ disagree
  - ☐ strongly disagree
  - ☐ I don't know
12. How willing are you to take risks, in general?
- ☐ 10 very willing
  - ☐ 9
  - ☐ 8
  - ☐ 7
  - ☐ 6
  - ☐ 5
  - ☐ 4
  - ☐ 3
  - ☐ 2
  - ☐ 1
  - ☐ 0 very unwilling

*[single-item on time preference]*

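### Age is asked only at Q8 and no on-screen stop is stated for a respondent who declares being under 18, so the written flow does not deliver the adults-only rule

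*Protocol*

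**What the plan says.** Section c) of the protocol sets the eligibility rule: "Only 18+ year-old participants can participate in the survey provided an informed consent". The entry step it describes is the consent click at question 1: "Participants are required to acknowledge their informed consent to enter the survey by clicking on the" OK button.

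Appendix 1 places age later, as "8. How old are you? Drop down menu". Q4, on how hormone therapy or surgery is paid for, comes before it and offers the answer "I'm doing sex work to afford it".

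Section p) explains that, besides the consent, "the question on the age includes the choice" of being under 18, and gives the consequence: "Respondents selecting this answer will be considered as non-qualifiers". The subsection Exclusion and Non-qualifiers lists the corresponding cases, among them "Not providing an age of 18 or higher" and "Not providing a numeric value for age". It also says that answers are recorded only when a module is completed and the respondent moves on. The subsection Non-respondents promises to report how many people failed the eligibility criteria.

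**The concern.** An adults-only rule needs a point in the flow where a person who says they are under 18 leaves the survey. The protocol describes a label for such people but no such point. If the text is implemented literally, someone who has just declared being a minor goes on to items on mood, physical assault and HIV testing. Depending on later answers, they may be offered items on unprotected sex, shared injecting equipment, paid sex and HIV stigma. Excluding the record afterwards protects the dataset but does nothing for the respondent.

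At stake are participant protection and the agreement between the stated eligibility rule and the instrument that ethics committees review. The survey's estimates are not affected.

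**Working it through.** No figure in the plan is to be reproduced. The check reads the item order and every printed routing note in Appendix 1 against the eligibility text.

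**Before the age item.** Q2 to Q7: 7 - 2 + 1 = 6 items, including Q4.

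**At the age item.** Q8 is printed as a drop-down menu with no routing note.

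**After the age item.** Two routing notes govern what follows.
- At Q45, those answering gay, bisexual or don't know are offered module 2 (Q46-Q60). Those answering lesbian or straight go to Q61.
- At Q61, those answering HIV-positive are offered module 3 (Q62-Q82).

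Neither note refers to Q8. The items shown after a declaration of being under 18 are therefore:

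| Route | Items | Count |
|---|---|---|
| Lesbian or straight, not HIV-positive | Q9-Q45 and Q61 | (45 - 9 + 1) + 1 = 38 |
| Lesbian or straight, HIV-positive | as above and Q62-Q82 | 38 + 21 = 59 |
| Gay, bisexual or unsure, not HIV-positive | Q9-Q61 | 61 - 9 + 1 = 53 |
| Gay, bisexual or unsure, HIV-positive | Q9-Q82 | 82 - 9 + 1 = 74 |

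**Items the protocol itself flags.** Section g) names the PHQ-4 (Q14-Q17), last HIV test (Q29), last partner's HIV status (Q48), comfort with attraction to men (Q58), own HIV status (Q61) and friends lost through disclosure (Q69). That is 4 + 1 + 1 + 1 + 1 + 1 = 9 items, all numbered above 8. A stop at Q8 would withhold all 9. Without one, 6 are shown on the shortest route (Q14-Q17, Q29, Q61) and all 9 on the longest.

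**Does the non-qualifier label imply a stop?** The list gives evidence both ways.
- It includes missing consent, which the Q1 click blocks at entry. So the label can cover people who are stopped live.
- It also includes people in no LGBTI group. They cannot be identified before Q45, and there a straight respondent is sent on to Q61 with no check of the sex and gender answers at Q2 and Q3. So the label also covers people whom the written flow carries forward.
- It includes people without a numeric age, so cases that pass Q8 without a valid answer are foreseen.

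The label alone therefore does not establish a stop, and no other text supplies one.

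**The case against.** The strongest reply is that the absence of a stop is read from silence. No sentence says that an under-18 respondent continues. A live survey tool can hold a disqualification step that a paper rendering does not print, and Appendix 1 does not even print the under-18 option, which is known only from section p). Section p) also presents the age question as an addition to the consent. The Q1 screen is not in the available copy, so any age statement there cannot be checked and its absence cannot be held against the plan. All of this stands.

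Exposure is also easily overstated. Section c) lets participants skip sensitive items, so Q4 is shown to a minor rather than necessarily answered. Modules 2 and 3 are offered, each with an exit button. Answers are recorded only for completed modules, so someone who leaves at Q8 has nothing recorded from Q2-Q7. These points stand too, and they make the counts maxima.

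A reader might go further and infer that the survey knowingly collects sexual and HIV data from minors, that they are relabelled only afterwards, or that section g) accepts the distress risk for adults alone. The documents support none of these. The first two depend on how the tool behaves, which is not described. Section g) speaks of respondents and study participants without naming an age.

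What the reply does not remove is that Q4 precedes the age item whatever the tool does at Q8, and that the protocol states no on-screen consequence for a declaration of being under 18.

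**Conclusion.** The point holds as a gap between the eligibility rule in section c) and the flow written in Appendix 1 and section p). Followed as written, a self-declared minor is shown 6 items before age is asked and between 38 and 74 after it, including at least 6 of the 9 items that section g) flags.

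This assumes that the printed routing is the whole routing, that nothing is skipped and that offered modules are accepted. An unwritten stop in the tool at Q8 would bring the later counts to zero but leave the 6 earlier items. An effective age check on the consent screen would reduce the number of minors who reach Q8. The number affected cannot be derived from the documents.

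The written flow should be corrected before the survey opens. No analysis result depends on it, because non-qualifiers are excluded in any case.

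**What to change.** - Ask age directly after the Q1 consent click.
- Route anyone who chooses under 18, or gives no age, to a closing page, with no further items shown or stored.
- Keep only the count of such respondents, which the subsection Non-respondents needs. The rule that answers are recorded only on module completion then needs an exception for this count.
- Reword section p) so that it states the routing as well as the non-qualifier label, and print the routing note beside the age item in Appendix 1.

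The cost is one item moved, one skip rule, and a closing page in each survey language. If age becomes Q2, then Q2-Q7 become Q3-Q8 and Q9 onward keep their numbers, so the existing reference to question 61 is unaffected. Adults who decline to give an age would now leave early, but they are already non-qualifiers.

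The downside is that a respondent who is routed out could restart and give a false age. Section p) already accepts that age cannot be verified.
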